### Data collection procedure

Both the questionnaire-based measures and accelerometer-measured physical activity will be completed at baseline and repeated at 3 months post-randomisation. Data will be assessed or extracted by a research assistant blinded to group allocation. Questionnaires will take approximately 30 min to complete and will be accessed via an online survey link (*REDCap* [36]) or sent in hardcopy by post, as preferred by the participant.

The intervention group will complete an additional questionnaire at 3 months post-randomisation to assess their impressions of the intervention, perceived benefits and barriers, adverse events, usage of goal setting and their physical activity plans following the intervention. The questionnaire will ask both open- and closed-ended questions, for example “Did you set yourself a physical activity-based goal during the study?” and “What, if anything, helped you to achieve your goals?” An email or phone call will be sent to any participants with incomplete outcome measures to improve data completeness and participant retention.

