### Recruitment

Participants will be recruited through advertising in newsletters and websites of community organisations, university and local health districts, via the study recruitment website, www.activewomenover50.org.au, word-of-mouth and social media. Participation is cost-free and no incentives are offered for participation. Potential participants will be screened for eligibility via an online survey. Recruitment commenced 3 May 2019, and at the time of submission of this manuscript, 66 participants had been recruited, 56 randomised and 0 participants had completed follow-up measures.

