### Control group

Participants randomised to the control group will be waitlisted to receive access to the *Active Women over 50* full programme after the 3-month follow-up data collection period.

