Intervention impact will be measured via a questionnaire and *Actigraph GT3X+* accelerometer, as detailed below, at 3 months post-randomisation assessing 1) the average number of steps taken per day (accelerometer measured), 2) the proportion of participants taking part in at least 150 min of moderate-intensity physical activity per week or at least 75 min of vigorous-intensity physical activity per week (as recommended by the Australian Physical Activity Guidelines) [5] (accelerometer measured), 3) exercise perceptions as measured by the *Exercise Benefits and Barriers Scale* [41], 4) mood as measured with the positive and negative subscales of the *Positive and Negative Affect Schedule* [42], 5) self-reported physical activity as measured by the *International Physical Activity Questionnaire* [43], 6) physical functioning as measured by the function component of the *Late Life Function and Disability Instrument* [44], and 7) health-related quality of life as measured by the *EQ-5D-5 L* survey [45].

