### Analysis of outcomes

Feasibility outcomes will be analysed descriptively to guide the design of a larger trial. Accelerometer data will be analysed using *ActiLife 6* software with time spent in different activity intensity levels calculated using the Troiano 2008 cut-points [47]. Acceptable wear time will be defined as at least 4 days with 10 h or more per day of valid wear time. Periods of 90 min or more of consecutive zeros (indicating non-use) will be considered as non-wear time.

Odds ratios will be calculated to assess the acceptability and feasibility of the study on the dichotomously scored primary outcome (the likelihood a participant would recommend participation in the study to someone else such as themselves) to assess the effect of group allocation on the dichotomously scored secondary outcome (proportion of people achieving physical activity in accordance with national guidelines) [5], adjusting for baseline scores. The study methods will be considered feasible if at least 80% of all participants complete follow-up measurements, or 80% of intervention participants access the intervention website or participate in the telephone health coaching session. Intervention versus control group differences in secondary outcomes, analysed with general linear models adjusting for baseline scores, will estimate effect sizes for sample size calculations for a larger trial and will provide an indication of likely intervention effect. This will be the progression criteria for proceeding to a fully powered randomised controlled trial.

A *p* value of < 0.05 will be considered statistically significant. Analyses will be pre-planned, conducted while masked to group allocation and will use an intention-to-treat approach. Analyses will be conducted using the *Stata 14* software package.

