### Sample size justification

There will be 60 community-dwelling females aged 50 years and over recruited for the pilot trial [48], allocated in equal numbers to the intervention and control groups. This sample size will provide feasibility data and estimates for sample size calculations for planning a future fully powered trial [49].

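### As the article describes it, only the intervention arm is asked about adverse events, so its count has no concurrent control rate, although controls complete a 3-month questionnaire anyway.

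*Protocol article*

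**What the plan says.** Data collection procedure describes two sets of instruments. The first is common to both arms: "Both the questionnaire-based measures and accelerometer-measured physical activity will be completed at baseline and repeated at 3 months post-randomisation". The second is for one arm only: the "intervention group will complete an additional questionnaire at 3 months post-randomisation to assess their impressions of the intervention, perceived benefits and barriers, adverse events", together with goal setting and later activity plans. This is the article's only mention of adverse events.

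The Secondary outcomes section gives the content of the common set. It begins "Intervention impact will be measured via a questionnaire and *Actigraph GT3X+* accelerometer, as detailed below, at 3 months post-randomisation" and then lists seven measures: steps, meeting the activity guideline, exercise perceptions, mood, self-reported activity, physical function and quality of life. The same section lists eight feasibility indicators taken from study records. Neither list has an adverse-event or safety item.

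Under Control group, controls are "waitlisted to receive access to the *Active Women over 50* full programme after the 3-month follow-up data collection period". They are therefore a concurrent group without programme access for the whole follow-up period.

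**The concern.** Aches, minor injuries and falls happen to insufficiently active women over 50 whether or not they are offered a programme. The article's own material reflects this: in Table 2 the website answers a question about longstanding pain, and falls prevention recurs in the messages and coaching. A 3-month recall question put to one arm would mix such background events with any that the programme causes. Randomisation is what would separate the two, and it helps only if both arms are asked the same question.

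The article is not silent on this point. It says who is asked, when, and on which form. That is a stated choice about ascertainment, not a detail left to a fuller document.

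What is at stake is modest but real. The pilot is meant to inform the design of a larger trial, and a harms form that differs by arm could be carried forward. The pilot would also pass on no background event rate for planning.

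**Working it through.** The article gives no adverse-event rate and no power calculation, so there is no figure of its own to reproduce. The check sets out what the plan as written can estimate, and then what two-arm collection would add.

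**Inputs from the article**
- Sample size: Sample size justification plans 60 women split equally between the two arms, so 60 / 2 = 30 per arm.
- Follow-up: the feasibility criterion in Analysis of outcomes is 80% of all participants. 0.80 × 60 = 48, or 24 per arm if losses are equal.
- Significance level: "A *p* value of < 0.05 will be considered statistically significant" (Analysis of outcomes). Sidedness is not stated; two-sided is assumed.

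**Assumed input:** 3-month event proportions of 5% to 30%.

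**1. As written: one proportion, in one arm.** At 10% and 30%, the expected number of intervention women with a background event is 0.10 × 30 = 3 and 0.30 × 30 = 9. Exact (Clopper-Pearson) 95% intervals with n = 30:

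| Women with an event | Proportion | 95% CI |
|---|---|---|
| 0 | 0% | upper limit 1 − 0.025^(1/30) = 11.6% |
| 3 | 10% | 2% to 27% |
| 6 | 20% | 8% to 39% |
| 9 | 30% | 15% to 49% |

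A risk difference needs a control proportion. None is collected, so none can be computed at any sample size.

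**2. If both arms are asked.** With equal true proportions p, the half-width of the 95% interval for the risk difference is 1.96 × √(2p(1 − p)/n). For p = 0.05 and n = 30: 1.96 × √(2 × 0.05 × 0.95 / 30) = 0.110.

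Power for a 20-point excess, with 30 per arm and two-sided 0.05, is Φ((0.20 − 1.96 × SE₀)/SE₁). SE₀ uses the pooled proportion and SE₁ the two separate proportions. For 10% against 30%: SE₀ = √(2 × 0.20 × 0.80 / 30) = 0.1033, SE₁ = √((0.09 + 0.21)/30) = 0.100, and Φ((0.20 − 0.2024)/0.100) = 0.49.

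| Control proportion | Half-width, 30 per arm | Half-width, 24 per arm | Power for +20 points |
|---|---|---|---|
| 5% | 11 points | 12 points | 59% |
| 10% | 15 points | 17 points | 49% |
| 20% | 20 points | 23 points | 39% |
| 30% | 23 points | 26 points | 35% |

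Two-arm collection therefore makes a comparison possible, but only a coarse one.

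**The case against.** Five points can be made for the plan.

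- **The article is condensed.** It names the outcome scales in the common questionnaire, not every item, and a full protocol or ethics file could provide for event reporting by everyone. Table 1 (item 4) also gives all participants email access to the trial manager. This stands as a limit: the point concerns the collection described here. An enquiry address is not systematic solicitation, though, and does not make ascertainment equal.
- **No safety comparison is promised.** Adverse events are not a primary, feasibility or impact outcome and do not enter the progression criteria. This stands in full, and it keeps the point from being more serious.
- **The item may be about the programme.** It sits beside impressions and perceived benefits, and its wording is not given. If it asks only about events that women link to the programme, fewer background events would be reported, and controls could not answer the same wording. This stands, and it is why the fix needs an arm-neutral item. Self-attribution does not replace a control rate.
- **The event rates are assumed.** They are. The absence of a control rate does not depend on them.
- **Sixty women cannot settle safety.** Correct, as the half-widths show.

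A reader might also infer that controls will show zero events by construction, so that any reported event makes the programme look harmful. The article does not support that. The control count is uncollected, not zero, and a descriptive one-arm count with no planned comparison need not be read as excess harm. It is simply hard to interpret.

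**Conclusion.** The point holds in a limited form. As described in this article, adverse events are solicited in one arm only, and the resulting count cannot be compared with background events, although a randomised comparison group is available and already fills in a 3-month form. It is an inexpensive improvement that should be made, not an error that invalidates the trial: no stated outcome, analysis or progression criterion changes.

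The lack of a control rate follows from the text alone, provided no other document adds collection in controls. The sizes quoted rest on 30 (or 24) women per arm and on assumed event proportions. It would go too far to say that two-arm collection would let this pilot establish safety. At equal assumed rates of 5–30%, 30 per arm leaves about 11 to 23 points either side of the estimate, which excludes only large excess harms.

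**What to change.** 1. Put one arm-neutral item in the common 3-month questionnaire for both arms, in the online and the hardcopy versions. It would ask about any fall, injury or other health event, with identical wording and recall period.
2. Keep the questions on programme attribution and impressions in the intervention-only form.
3. Report counts and proportions by arm descriptively. If a risk difference is given, show its 95% CI and state that about 30 per arm can exclude only large excess harms.
4. If another study document already provides for event collection in controls, say so in the protocol and confirm that the method and timing are the same in both arms.

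The cost is about a minute more for some 30 controls and a minor ethics amendment. At submission the change could still cover everyone: the Recruitment section reports "56 randomised and 0 participants had completed follow-up measures".

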### Objectively measured physical activity

*Actigraph GT3X+* is able to accurately estimate how physically active a person is throughout the day by measuring 3D body accelerations and is a valid instrument that has been extensively researched in the physical activity and public health field [46]. Participants will wear the *Actigraph (GT3X+)* for 7 consecutive days during waking hours (except during water-based activities or bathing). The accelerometer will be posted to participants with instructions for usage, along with an activity calendar to complete over the 7-day period and a pre-paid envelope for returning the device to the research team. Activity counts will be collected at a sampling frequency of 30 Hz and reintegrated to 60-s epochs for data analysis. Accelerometer data will be manually checked against participant activity calendars to verify wear time, and erroneous data will be excluded prior to analysis.

### Data management

To ensure participant confidentiality, the final dataset will contain re-identifiable information only. All study data will be entered onto a password-protected database and maintained on a firewall-protected local network server at The University of Sydney. Paper files will be stored in a locked filing cabinet in the Chief Investigator’s office. The database and paper files will only be accessed by study staff. All publications associated with the results of the study will involve de-identified data, so participant confidentiality will be maintained.

### Analysis of outcomes

Feasibility outcomes will be analysed descriptively to guide the design of a larger trial. Accelerometer data will be analysed using *ActiLife 6* software with time spent in different activity intensity levels calculated using the Troiano 2008 cut-points [47]. Acceptable wear time will be defined as at least 4 days with 10 h or more per day of valid wear time. Periods of 90 min or more of consecutive zeros (indicating non-use) will be considered as non-wear time.

Odds ratios will be calculated to assess the acceptability and feasibility of the study on the dichotomously scored primary outcome (the likelihood a participant would recommend participation in the study to someone else such as themselves) to assess the effect of group allocation on the dichotomously scored secondary outcome (proportion of people achieving physical activity in accordance with national guidelines) [5], adjusting for baseline scores. The study methods will be considered feasible if at least 80% of all participants complete follow-up measurements, or 80% of intervention participants access the intervention website or participate in the telephone health coaching session. Intervention versus control group differences in secondary outcomes, analysed with general linear models adjusting for baseline scores, will estimate effect sizes for sample size calculations for a larger trial and will provide an indication of likely intervention effect. This will be the progression criteria for proceeding to a fully powered randomised controlled trial.

A *p* value of < 0.05 will be considered statistically significant. Analyses will be pre-planned, conducted while masked to group allocation and will use an intention-to-treat approach. Analyses will be conducted using the *Stata 14* software package.

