### Outcomes

#### Primary outcomes

The primary outcome will be participant acceptability of the intervention and study methods. A global measure will assess whether participants would recommend participation in the study to someone else like themselves. Participants will be asked to select “yes” or “no/unsure” to the question “Would you recommend the *Active Women over 50* study to another person such as yourself?” at 3 months post-randomisation.

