## Discussion

Active ageing is at the core of this highly innovative project that targets women aged 50 years and older. To our knowledge, there currently exists no other programme that specifically targets physical activity information, resources and support in a way that is relevant to the needs of women aged 50 years and over who are insufficiently physically active.

This innovative programme takes a tailored and supported approach to the provision of physical activity information and follow-up support through health coaching and email or SMS messaging and has the potential to substantially increase physical activity participation in women people aged 50 years and over. End user input has been used to design the website to provide relevance and familiarity to the target audience in the delivery of information, resources, inspirational stories and suggestions. Participants are regularly referred to the website via email or SMS messaging and provided with health coaching to further tailor and support their uptake of regular physical activity.

The *Active Women over 50* programme also allows for the targeting of key messages to a broad range of women aged 50 years and over from different geographical areas and sociodemographic backgrounds. If found to be feasible and acceptable in this pilot RCT and effective in a future planned, rigorously conducted RCT, the *Active Women over 50* programme has the potential to be easily scalable and implemented widely to significantly impact the lives of many people.

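### The 80% feasibility rule joins follow-up and uptake with *or*, so either can stand in for the other, and the progression rule sets no level for the primary outcome

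*Protocol article*

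**What the plan says.** Analysis of outcomes gives the only numerical feasibility thresholds in the article. The condition for feasible study methods is "at least 80% of all participants complete follow-up measurements, or 80% of intervention participants access the intervention website or participate in the telephone", where the last item is the coaching call. The next sentence concerns between-group differences in secondary outcomes, which are to supply effect sizes for a larger trial and an indication of the likely effect. Then comes "This will be the progression criteria for proceeding to a fully powered randomised controlled trial".

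The Primary outcomes section states "The primary outcome will be participant acceptability of the intervention and study methods". It is measured at 3 months by one question on recommending the study to someone similar, answered yes or no/unsure. Its planned analysis is given as "Odds ratios will be calculated to assess the acceptability and feasibility of the study on the dichotomously scored primary outcome", with no level that would count as acceptable. The Discussion makes the programme's prospects conditional on both properties: "If found to be feasible and acceptable in this pilot RCT and effective in a future planned, rigorously conducted RCT".

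Sample size justification fixes the denominators: "There will be 60 community-dwelling females aged 50 years and over recruited for the pilot trial", allocated equally to the two groups.

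**The concern.** The two sides of the first *or* measure different things. Follow-up completion, in both arms, shows whether a larger trial could collect its 3-month questionnaire and accelerometer data. Website access and coaching uptake, in the intervention arm only, show whether the programme reaches women. Neither can make up for a failure of the other, and website access says nothing about retention in the wait-list arm, which has no website access during follow-up. Followed as written, the rule can call the methods feasible when most of the evidence on one of these two questions is unfavourable.

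The decision on whether and how to proceed is the main product of a feasibility pilot, so a loose connective matters here more than it would in a descriptive passage. Two further gaps bear on the same decision. The progression sentence does not make clear which preceding statement it refers to. The primary outcome, which the Discussion treats as a condition for going on, enters with no threshold.

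**Working it through.** **Inputs from the article.** 60 women, 30 per arm (Sample size justification); the 80% thresholds (Analysis of outcomes). The article gives no expected rates for follow-up, website access or coaching, so all true rates below are assumptions. The sample size is stated without power or precision inputs, so there is no stated figure to reproduce.

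**Thresholds as counts.** Follow-up: 0.80 × 60 = 48 of 60. Uptake: 0.80 × 30 = 24 of 30.

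**Logic, with no assumed rates.** If 24 of the 30 intervention women access the website, the second limb is met on any reading of it. Because of the first *or*, the rule is then met at every follow-up count from 0 to 60. Conversely, 48 of 60 completing follow-up meets the rule if no one uses the website or takes the call.

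**Illustration.** Exact binomial upper tails:

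| True rate | P(≥48 of 60) | P(≥24 of 30) |
|---|---|---|
| 50% | <0.001 | 0.0007 |
| 60% | 0.0008 | 0.017 |
| 70% | 0.057 | 0.160 |
| 80% | 0.576 | 0.607 |
| 90% | 0.994 | 0.974 |

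- *Poor follow-up, good website access.* Follow-up 60%, website 90%: website access alone meets the rule with probability 0.974, and follow-up with probability 0.0008. Since any one limb is enough, the rule passes at least 0.974 of the time however the indicators are correlated.
- *Good follow-up, poor uptake.* Follow-up 90%, website and coaching each 50%: follow-up alone passes with probability 0.994.

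**One composite or two criteria.** The uptake limb carries a single 80% and reads naturally as a composite: the woman did either. If website and coaching are each 70% and independent, composite uptake is 0.70 + 0.70 − 0.49 = 0.91 and P(≥24 of 30) = 0.985. With follow-up also at 70%, the rule as written passes with probability 1 − (1 − 0.057)(1 − 0.985) = 0.986. Requiring both limbs gives 0.057 × 0.985 = 0.056. The composite reading therefore makes the second *or* a legitimate definition of uptake, but leaves the effect of the first *or* in place.

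**Pass rate if the first *or* becomes *and*** (independence assumed between follow-up and uptake):

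| True rates | Follow-up and composite uptake | Follow-up, website and coaching separately |
|---|---|---|
| each 80% | 0.576 × 1.000 = 0.576 (composite 0.96) | 0.576 × 0.607 × 0.607 = 0.212 |
| each 90% | 0.994 × 1.000 = 0.994 (composite 0.99) | 0.994 × 0.974 × 0.974 = 0.944 |

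The composite column also takes website and coaching as independent within a woman. If the same women did both, composite uptake would equal the single rate: 0.576 × 0.607 = 0.350 at 80%, and 0.994 × 0.974 = 0.969 at 90%.

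**The case against.** The 80% sentence is about when the study methods are feasible. The progression sentence comes after the effect-size sentence and may refer to that, to the thresholds, or to the whole paragraph. It is therefore not established that the 80% rule alone decides progression. This stands. But the effect-size sentence carries no threshold, so on that reading there would be no usable progression criterion, and the reference needs clarifying either way.

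A reader might infer that the rule has three interchangeable 80% criteria, each sufficient. The text does not settle that: the single 80% for uptake supports a composite at least as well. Only the first *or* is a defect on both readings.

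A reader might also infer that the trial would go forward whatever women say about recommending it. The article does not support this. It plans an analysis of the primary outcome and makes the programme's future depend on acceptability as well as feasibility. What is missing is a level. Likewise, the view that opening the website once would count as access is not in the article: access is left undefined in the rule, and the Secondary outcomes section records content and intensity of use as well.

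Finally, feasibility outcomes will be reported descriptively, so poor follow-up would be visible to those who decide. That is true, and it softens the practical consequence. It does not repair a stated rule that would label such a result feasible. The assumed rates are illustrative, and independence is doubtful because the indicators arise in the same women. The logical point needs neither.

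**Conclusion.** The concern holds in this form: as worded, the feasibility rule lets uptake stand in for follow-up and the reverse, and followed exactly it can give a wrong feasibility conclusion. With assumed true follow-up of 60% and website access of 90%, it is met with probability of at least 0.97, against less than 0.001 for the follow-up criterion. That contrast rests on the planned 60 and 30, on the assumed rates and on binomial sampling, but not on independence. The defect in the wording rests on no assumption.

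Two related defects are ones of clarity: the unclear reference of the progression sentence, and the absence of a stated level for acceptability. The documents do not show that three separate criteria were intended, nor that acceptability would be ignored. The *or* may be a slip for *and*, but nothing in the article says so.

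**What to change.** 1. Replace the first *or* with *and*: feasibility requires at least 80% of all participants completing follow-up and at least 80% uptake in the intervention group.
2. State whether website access and coaching form one composite or two separate criteria.
3. Say explicitly that the progression criteria are these thresholds, and separate them from the effect-size sentence.
4. Add to the progression rule the proportion answering yes to the recommendation question as worded under Primary outcomes, at a level the sponsor fixes before outcome data are seen. The documents give no basis for a particular level, so none is proposed here. When the article was submitted, 56 women had been randomised and none had completed follow-up measures (Recruitment section), so the level could at that point have been set without knowledge of results.

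The change is to wording only and needs no new data. The cost is a stricter gate. Follow-up plus composite uptake passes about 58% of the time when follow-up, website and coaching rates are each truly 80% and independent (35% if website and coaching users are the same women), and about 99% when each is 90% (97% in the same-women case). Treating website and coaching as two required criteria lowers these to about 21% and 94%. An acceptability level would lower them further, by an amount that depends on the level chosen.

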**Methods:**

Sixty community-dwelling women who are insufficiently active according to national guidelines, will be recruited and randomised to 1) receive the *Active Women over 50* programme or 2) a wait-list control. *Active Women over 50* is a 3-month physical activity programme guided by behaviour change science, providing access to a website, one telephone-delivered health coaching session from a physiotherapist and 8 email or 24 SMS messages. The primary outcome is the proportion of participants at 3 months post-randomisation who would recommend participation in the programme to another person like themselves. Secondary outcomes are feasibility measures: rates of recruitment, retention, completeness of outcome data and uptake of telephone support; and intervention impact measures: accelerometer-assessed average steps/day, proportion of participants meeting national guidelines on moderate to vigorous physical activity; and questionnaire-assessed quality of life, exercise perceptions, mood, physical functioning and self-reported physical activity. Intervention participants will also complete a follow-up survey to assess impressions of the intervention and adoption of strategies for physical activity participation. Data will be analysed descriptively to guide the design of a larger trial. Between-group differences in secondary outcomes will be used to estimate effect sizes for sample size calculations for a fully powered randomised controlled trial.

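### Between-group differences from a 60-woman pilot are to size the larger trial, and can be read as the basis for progression, but are too imprecise for either use

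*Protocol article*

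**What the plan says.** The use of the effect estimates is stated twice. The abstract's Methods paragraph says: "Between-group differences in secondary outcomes will be used to estimate effect sizes for sample size calculations for a fully powered randomised controlled trial". In "Analysis of outcomes", the group differences come from linear models with baseline adjustment, and their stated purpose is that they "will estimate effect sizes for sample size calculations for a larger trial and will provide an indication of likely intervention effect".

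The sentence that follows in "Analysis of outcomes" is: "This will be the progression criteria for proceeding to a fully powered randomised controlled trial". No threshold for an effect is given. The only numerical thresholds in that paragraph are the 80% figures for feasibility, one sentence before the effect-size sentence. The next paragraph adds a general convention for p-values ("value of < 0.05 will be considered statistically significant"), and it does not exempt the group comparisons.

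"Sample size justification" gives the recruitment target ("There will be 60 community-dwelling females aged 50 years and over recruited for the pilot trial") with a 1:1 split. It then states what that number is for: "This sample size will provide feasibility data and estimates for sample size calculations for planning a future fully powered trial". The number rests on two citations. The article states no effect size, standard deviation, power or precision target for it.

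**The concern.** A pilot of this size can estimate a standard deviation or a retention rate well enough to plan with. It cannot do the same for a treatment effect. Required sample size varies with the inverse square of the assumed difference, so error in the estimated effect is magnified when it becomes a sample size. If the stated rule is followed, the size of the larger trial is set mainly by sampling error in the pilot. Some plans would be far too small, some unworkably large, and some could not be made because the estimate has the wrong sign.

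The progression sentence adds a second problem. If its opening word refers to the effect estimates, the decision to proceed rests on the same noisy quantity, with no stated cut-off.

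**Working it through.** **No figure to reproduce.** The 60 women come with no power or precision inputs, so I checked how precise the planned comparison would be.

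**Inputs from the protocol article.** 60 women, 1:1, so 30 per arm; adjustment for baseline; significance level 0.05, taken as two-sided. The 80% follow-up threshold in "Analysis of outcomes" is used as a low case: 0.8 × 30 = 24 per arm.

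**Assumptions not in the documents.** True effect 0.3 SD; baseline–follow-up correlation r = 0.6; 80% power for the larger trial; normally distributed estimates.

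**1. Precision.** SE = √(1 − r²) × √(2/n); half-width = 1.96 × SE.

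| n per arm | r | SE | 95% half-width |
|---|---|---|---|
| 30 | 0.6 | 0.8 × 0.258 = 0.207 | 0.40 SD |
| 24 | 0.6 | 0.8 × 0.289 = 0.231 | 0.45 SD |
| 30 | 0 | 0.258 | 0.51 SD |
| 24 | 0 | 0.289 | 0.57 SD |

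Every half-width exceeds the assumed effect.

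**2. Wrong-sign pilots (r = 0.6).** Φ(−0.3/0.207) = 0.07 with 30 per arm; Φ(−0.3/0.231) = 0.10 with 24.

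**3. Planned size of the larger trial (r = 0.6).** n per arm = 2 × (1.96 + 0.8416)² × (1 − 0.36)/d² = 10.05/d². The true effect of 0.3 needs 10.05/0.09 = 112 per arm. An observed 0.5 gives 41 and an observed 0.1 gives 1,005. Without baseline adjustment the same three effects (0.3, 0.5, 0.1) need 175, 63 and 1,570. The 25-fold spread between 0.5 and 0.1 is the same.

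Suppose every positive estimate is used (30 per arm). The 10th to 90th percentile of planned size corresponds to estimates of about 0.574 and 0.0995 SD: 10.05/0.574² ≈ 31 and 10.05/0.0995² ≈ 1,015 per arm. Simulation gives 31 and about 1,006. I summarise this as 31 to about 1,000.

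**4. True power of those plans.** For an observed effect d, true power = Φ(0.3 × 2.80/d − 1.96).
- It is under 80% whenever d > 0.3. As a share of positive pilots this is 0.50/0.927 = 54% (30 per arm) and 0.50/0.903 = 55% (24 per arm).
- It is under 50% whenever d > 0.3 × 2.80/1.96 = 0.43. This is 0.266/0.927 = 29% and 0.289/0.903 = 32%.
- Mean true power by simulation (400,000 pilots) is 0.71 with 30 per arm and 0.69 with 24.

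**5. A hypothetical gate.** If only pilots with p < 0.05 in the intervention's favour went forward, which the article does not say, the estimates would average about 0.54 SD (30 per arm) to 0.60 SD (24 per arm). Mean true power would be about 37% and 31% respectively.

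**6. What the pilot can estimate.** The 95% interval for a pooled standard deviation is about 0.85 to 1.22 times the estimate with 60 women, and 0.83 to 1.26 with 48. If 48 of 60 complete follow-up, the exact 95% interval is 67.7% to 89.2%.

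**The case against.** The strongest reply is that, without selection, the pilot estimate is unbiased. Sizing on every positive estimate gives mean true power of about 0.7, which is short of 0.80 but not a collapse. This stands, and it is why the 31–37% figure can only be shown as a hypothetical. It does not rescue the plan, because an average of 0.7 covers trials planned at 31 per arm and at about 1,000 per arm.

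Several stronger readings are tempting, but the text does not support them.
- A reader might infer that the programme will be abandoned if p > 0.05, or pursued only if the effect looks promising. The significance level is a general convention in a separate paragraph. Nothing ties it to progression or to sizing.
- A reader might infer that progression is definitely decided on the effect estimates. The sentence could equally refer to the 80% thresholds, or to both. What can be shown is ambiguity.
- A reader might see a contradiction between the abstract's descriptive analysis and a significance level. "Analysis of outcomes" applies the descriptive approach to feasibility outcomes, so the two can be read together.
- A reader might add a multiplicity charge for the seven impact outcomes. Any figure would need independent tests, yet three of the seven measure physical activity, and the article plans no claim of efficacy.

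"Sample size justification" does not say that the estimates it mentions are treatment effects; they could be standard deviations or retention. It is weaker support than the abstract and "Analysis of outcomes". Nor does anything in the article prevent the sponsor from choosing an important difference later. It does, however, state a different source.

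**Conclusion.** The concern holds in limited form. The article commits to using observed group differences to size the larger trial, and its progression sentence can be read as resting on them too. With 24–30 analysed per arm those differences are too imprecise for either purpose. Under a true effect of 0.3 SD and a correlation of 0.6, just over half of the resulting plans would fall below 80% power and about three in ten below 50%.

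The exact figures depend on those assumptions. A larger effect with a stronger correlation would help: at 0.5 SD, r = 0.7 and full retention, the pilot's own power is about 77%, though the interval is still about ±0.37 SD. The 60 women are not the fault, since that number is reasonable for feasibility and for estimating variability. The fault is the use planned for the effect estimates. Participants are unaffected; the pilot's planning purpose is what suffers. The change should be made.

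**What to change.** Reword the abstract's Methods paragraph, "Analysis of outcomes" and "Sample size justification" as follows.

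1. Say that progression rests on the acceptability and feasibility criteria only, and name them in the progression sentence so that its subject is no longer open.
2. Say that the larger trial's target difference will come from a prespecified minimum important difference, for example in steps per day.
3. Limit what the pilot supplies to the standard deviation, the baseline–follow-up correlation, the control-arm proportion meeting guidelines, and retention. Allow for uncertainty in the standard deviation. One convention is its one-sided 80% upper limit, about 1.09 times the estimate with 60 women and 1.10 with 48.
4. Report between-group differences with 95% confidence intervals, labelled exploratory, and remove the 0.05 significance rule.

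The cost is wording only, with no change to recruitment, measurements or the 60 women. "Recruitment" reports that no participant had completed follow-up at submission, so at that point the change could have been made before any outcome was seen. The real burden is that the sponsor must choose and defend an important difference for the next trial.
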